## Abstract

**Background:**

Neurofeedback has been applied effectively in various areas, especially in the treatment of children with attention-deficit/hyperactivity disorder (ADHD). This study protocol is designed to investigate the effect of slow cortical potential (SCP) feedback and a new form of neurofeedback using near-infrared spectroscopy (NIRS) on symptomatology and neurophysiological parameters in an adult ADHD population. A comparison of SCP and NIRS feedback therapy methods has not been previously conducted and may yield valuable findings about alternative treatments for adult ADHD.

**Methods/Design:**

The outcome of both neurofeedback techniques will be assessed over 30 treatment sessions and after a 6-month follow-up period, and then will be compared to a nonspecific biofeedback treatment. Furthermore, to investigate if treatment effects in this proof-of-principle study can be predicted by specific neurophysiological baseline parameters, regression models will be applied. Finally, a comparison with healthy controls will be conducted to evaluate deviant pretraining neurophysiological parameters, stability of assessment measures, and treatment outcome.

**Discussion:**

To date, an investigation and comparison of SCP and NIRS feedback training to an active control has not been conducted; therefore, we hope to gain valuable insights in effects and differences of these types of treatment for ADHD in adults.

**Trial registration:**

This study is registered with the German Registry of Clinical Trials: DRKS00006767, date of registration: 8 October 2014.

## Background

Attention-deficit/hyperactivity disorder (ADHD) is one of the most common disorders of childhood with a cumulative incidence of up to 7.5% by 19 years of age [1]. The primary symptoms of ADHD include inattentiveness, impulsivity, and hyperactivity, which persist into adulthood for a large proportion of children diagnosed with this disorder. The estimated prevalence of clinician-assessed adult ADHD in general and clinical populations is 4 to 5% and 7.5%, respectively [2,3]. Impairments in educational, occupational, neuropsychological and social functioning are observed [4]. Psychiatric comorbidities are highly prevalent in the adult ADHD population and include mood, anxiety, and substance abuse disorders [5].

Various findings indicate that ADHD has its origin in neurobiological dysfunctions including a major genetic component in etiology [6,7], specifically in relation to the regulation of the dopaminergic neurotransmission [8]. Relative to controls, ADHD adults have a significant reduction in orbitofrontal volumes in the left hemisphere [9], overall cortical gray matter reduction in prefrontal and anterior cingulum cortices [10] and volume reductions in the cerebellum [11]. On a functional level, a dysfunction of the prefrontal cortex (PFC) has been assumed to underlie many of the deficits observed in ADHD, with particular involvement of the dorsolateral prefrontal cortex (DLPFC) and cingulate areas (for example, [12]). Electroencephalography (EEG) studies comparing adult individuals with ADHD to healthy controls have identified a variety of brain activity patterns including increased theta/beta ratios [13,14], increased theta and alpha activity [15,16], and deviant activity in delta and beta frequencies [17]. However, brain activity patterns seem to be dependent on the ADHD subtype [18]. Event-related potentials (ERP) also differ between adult ADHD and healthy control populations, with adult ADHD patients showing enhanced N100 and N200 and decreased P300 activity [19,20] together with topographic differences in P100 and P200 [21] and P300 [22]. Additionally, altered error potentials indicate deficits in conflict monitoring [23]. Rockstroh *et al*. [24] observed impaired regulation of slow cortical potentials (SCP), a specific type of ERP in which slow direct current shifts reflect the excitation threshold of large cortical cell assemblies in children with attention problems. SCP shifts in the electrically negative direction reflect a reduction of the excitation threshold, whereas shifts in the electrical positive direction reflect an increase of the excitation threshold. These studies show the suitability of EEG/ERP recordings for measuring cortical dysregulation during resting and task conditions for participants with ADHD.

Looking at corresponding neuropsychological concepts, ADHD has repeatedly been associated with a disturbance of single or multiple executive functions such as selective and divided attention and working memory. Consequently, there have been various attempts to determine intermediate phenotype markers based on measures grounded in neuroscience [25-27]. In spite of considerable differences between the various intermediate phenotype models, deficits in executive functioning have been demonstrated in most of them and have repeatedly been suggested to underlie the disease (for example, [28]). Specifically, deficits in working memory, response inhibition, and cognitive response control have been identified in both ADHD participants and their unaffected relatives, and have therefore been suggested as cognitive intermediate phenotypes of ADHD [25,29,30].

A method optimally suited to assess the cortical aspect of these deficits is near-infrared spectroscopy (NIRS), an optical imaging method, which allows for noninvasive *in vivo* measurements of changes in the concentration of oxygenated (O2Hb) and deoxygenated (HHb) hemoglobin in brain tissue [31-33]. NIRS has repeatedly been cross-validated using, for example, blood-oxygen-level dependent (BOLD) and arterial spin labeling-based functional magnetic resonance imaging (fMRI) [34,35], confirming the physiological basis of the signal. In a NIRS study, poorer performance in a working memory task was observed for adult participants suffering from ADHD compared to healthy controls [36]. The tendency for more omission errors during a 2-back task was also associated with significantly reduced prefrontal activation in the ADHD group compared to healthy controls. Using another executive control task, prefrontal deficits in adult ADHD participants were again observed, even when no overt performance differences occurred [37]. These studies show the suitability of NIRS in measuring prefrontal control deficits during tasks of executive function in participants with ADHD.

In neurofeedback treatment, participants learn to regulate their own brain activity (for example, SCP, EEG oscillations, O_2_Hb concentration, *etcetera*) using online feedback. The training is based on an operant conditioning process in which only the desired brain activity is rewarded. As stated previously, Rockstroh *et al*. [24] observed impaired regulation of SCP and reduced negativities in anticipation of a task in children with attentional problems. Helps *et al*. [38] found that ADHD children exhibited decreased resting state very low frequency power (0.1 Hz) and attenuated power during rest-task transitions that varied significantly from healthy controls. Attenuation of power was negatively correlated with task performance, whereby participants who attenuated least made more errors, had greater variability, and slower reaction times (RT). These findings support the conceptualization of ADHD symptoms as impaired excitation threshold regulation, characterized by decreased cortical negativity. Therefore, it was hypothesized that training ADHD participants to augment negative SCP would increase the capacity to produce cortical activation necessary for concentration and cognitive tasks.

The use of SCP as a treatment parameter for children with ADHD has yielded significant reduction in ADHD symptoms, improved attention [39-41], and has produced changes in ERP, most importantly for SCP feedback of the contingent negative variation (CNV) (for example, [40,42]). A recent study by Studer et al. [43] with healthy adult participants found increased CNV amplitude after SCP feedback training. Examination of EEG during SCP-treatment indicated that children with ADHD are able to control SCPs and this skill was observed to be stable two years after the end of treatment [44]. Therefore, one of the potential advantages of neurofeedback therapy over pharmacological treatment strategies might be the stability of improvements beyond the intervention period. As this has been shown to be an effective treatment for children, we would like to investigate whether SCP feedback is an efficient treatment for adult ADHD participants as well.

In recent years, some efforts have been made to extend neurofeedback applications from the electrophysiological to a broader neuroimaging domain. Functional imaging methods such as fMRI have the advantage of a superior spatial resolution (compared to EEG), theoretically allowing for neurofeedback training of circumscribed brain areas. Investigation of fMRI feedback has subsequently shown that healthy adult subjects are able to quickly learn to self-regulate brain activity on the basis of the BOLD signal [45-47]. As NIRS and fMRI both measure the regulation of the blood metabolism, we expect similar findings with NIRS feedback. As NIRS is relatively insensitive to motion artifacts and allows measurements to be performed in a natural, relaxed sitting position, it might provide an interesting alternative to fMRI for feedback training in psychiatric disorders such as ADHD. To date, only a few studies have attempted to use functional near-infrared spectroscopy (fNIRS) with a neurofeedback protocol [48]. In a pilot project, real-time feedback was provided to train subjects to increase their motor cortex activation using motor imagery. It was shown that the signal-to-noise ratio of the O_2_Hb signal increased significantly over the course of the feedback training within five sessions. In another study, 21 subjects performed motor imagery with relevant cortical feedback and sham feedback. Only in the “verum” feedback condition has greater activation of the contralateral premotor cortex been induced [49].

Based on this preliminary work, we want to investigate the efficacy and long-term stability of fNIRS feedback in comparison with EEG feedback.

Additionally, neurophysiological predictors of treatment outcome will be investigated. Target parameters of the baseline NIRS and EEG assessments will be used as predictors in regression analyses. Based on previous findings regarding the prediction of treatment outcome via EEG markers of frontal lobe function in schizophrenic patients [50], we expect treatment effects to be particularly pronounced in participants with weak activation in the baseline frontal lobe assessments, especially for the NIRS feedback arm that is specifically focused on strengthening frontal lobe function. Regarding the EEG baseline data, mean relative theta and relative beta power as well as theta/beta ratios will be calculated for frontal and central regions of interest (ROI) during the eyes open and eyes closed resting state conditions. Additionally, P300 and CNV amplitudes and latencies will be calculated during neuropsychological assessment. Research indicates that adult ADHD participants possess elevated theta/beta ratios [13,14], which have been found to discriminate ADHD participants from healthy control populations [51,52]. These ratios may have prognostic value for prediction of outcome after stimulant medication as well as after neurofeedback treatment [18]. Elevated theta/beta ratios are hypothesized to reflect task-related brain “activation” and serve as a discriminant of behavioral performance [53]. Dominant slow wave activity has been linked with reduced auditory oddball P300 activity [54] and stimulant medication response [52], while larger pre-training CNV activation has been linked with larger symptom reductions following SCP feedback [55]. Therefore, we expect effects to be particularly pronounced in participants with elevated theta/beta ratios and decreased P300 amplitude but greater CNV negativity at baseline assessment.

## Methods/Design

In this proof-of-principle study, a total of 60 adult participants diagnosed with ADHD (combined, hyperactive, or inattentive type) are randomly blockwise assigned to SCP, NIRS, or electromyogram (EMG) feedback groups (n = 20 each) stratified for age, sex, and educational level. This is the first study to investigate and compare the efficacy of these treatment modalities in an adult ADHD population.

Twenty healthy controls matched for age, sex, IQ, and pre- and post-treatment duration will be included in the neurophysiological assessments for pre- and post-treatment measurement in order to establish “expected” activation patterns and allow for a more thorough interpretation of changes following the neurofeedback treatment. The study objectives are as follows:Assess whether there are physiological differences (EEG and ERP) in ADHD participants compared to healthy controls.Assess whether adult participants are able to demonstrate learning of cortical self-regulation.Assess whether treatment leads to an improvement in cognition (that is, attention and working memory) and behavior (that is, restlessness and impulsivity), and changes in specific EEG or NIRS parameters.Assess whether specific methods and protocols are more efficacious in changing behavioral, cognitive, and EEG and NIRS outcome variables.Assess whether changes are stable at the 6-month follow-up.Assess whether specific methods and protocols differ in the stability of cortical self-regulation and clinical effects at the 6-month follow-up.Assess whether the efficiency of the different training protocols differs depending on individual neurocognitive baseline parameters (for example, frontal lobe activation during neuropsychological assessments; baseline CNV etc.).

### Study flow

At baseline/pre-treatment, participants are screened and diagnosed with ADHD, assessed with a battery of neuropsychological questionnaires for evaluation of cognitive and behavioral outcome variables, and evaluated using a 22-channel NeXus-32 (Mind Media B.V. with Biotrace^+^ Software, Herten, The Netherlands) continuous EEG recording (eyes closed, eyes open, auditory oddball, and auditory Go/NoGo task). Moreover, concentration changes of O_2_Hb and HHb during three executive functioning tasks (working memory, Go/NoGo, and word fluency) are measured by a 52-channel continuous wave NIRS-system (ETG-4000, Hitachi Medical Co., Tokyo, Japan). At mid-treatment (that is, after 15 sessions), post-treatment (after 30 sessions), and 6-month follow-up, the neuropsychological assessments are repeated.

Healthy controls (n = 20) undergo the EEG/NIRS assessment for the pre- and post-treatment measurement points. See Figure 1 for an illustrated overview of the study flow.

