### Ethics and written consent

This study (DRKS00006767) was approved by the local Ethics Committee (Ethics Committee for the Medical Department, University of Tübingen, Germany, Ethics votum number: 434/2010B01; Date 15 October 2012) according to the Declaration of Helsinki. Before entering the study, participants are informed about the study objectives, study design, and potential risks by one of the main investigators and are given this information in writing. Written consent is obtained from all participants.

Study-related information and informed consent is administered by the investigator(s) to ensure that participant questions and concerns are addressed. Participants receive the following information designed to educate him/her extensively on the subject of the investigation: information regarding the overall study; information on the goals, methods, and procedures of the study; and the end of the study plan. Participants are informed that they have the right to discontinue their participation at any time without giving a specific reason and without penalty.

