**Figure 2 Fig2:**
[figure not shown]
Neurofeedback trial set-up: 2sec baseline, 8sec active phase and 2sec reinforcement phase.

Participants are trained one to three times per week (maximum of five times per week) for a total of 30 sessions. Each session lasts about an hour, including the preparation time and is divided into four 8-min blocks. To generalize newly acquired regulation skills to everyday life situations, the third block in each session serves as “transfer block” in which no visual feedback is presented during the active feedback phase of each trial. The level of success is indicated with the visual reward system only. Participants are instructed to use their self-regulation in everyday life situations. After the 15th session, participants are provided with a 15 × 5 inch picture of the neurofeedback screen as a memory aid as well as a CD playing a video of the transfer trials without feedback to help the transfer to daily life.

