### Control group

The healthy controls undergo only part of the diagnostic procedure, including the ADHD-SB, BDI, STAI, EHI, BSL, d2, CFT-20-R (see section below for explanation), demographic and medical history questionnaires, and the EEG and NIRS assessment. The controls are assessed at two time points but do not receive any treatment in between. The first measurement is being performed directly after the recruitment and screening procedure. The time between the first and the second measurement is dependent on the amount of time it takes the matched patient to complete treatment (+/− two months).

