### Randomization and blinding

The randomization is conducted in two steps: first a blockwise randomization, and second a pairwise randomization for age, sex and IQ. We determined a grouping order (EEG = 1; NIRS = 2; and EMG = 3). If the participant does not fit into group 1, he/she is matched to group 2 and if not group 2, then group 3. For the next participant, the matching process starts in group 2 and so forth.

The participants are not blinded to the treatment condition, as it is easier to achieve physiological self-control knowing which parameter has to be controlled. Further, blinding was not possible, due to the different feedback methods that made it obvious which treatment was being applied and received (for example, NIRS vs. EEG measurement setup). The different methods are used in different labs and with different technical requirements, and therefore, neither blinding of participants nor blinding of assessors was possible.

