### Statistical analysis

#### Electroencephalogram, near-infrared spectroscopy, electromyogram and behavioral data

All dependent variables will be tested for effects within and between groups by an analysis of variance (ANOVA) (three groups x four assessment points). For the comparison of pretest-data between ADHD and healthy subjects, t-tests and/or one-way ANOVAs will be applied. If normal distribution cannot be assumed, non-parametric tests will be used.

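### Mid and post assessments are timed only by completed sessions, so early stoppers have no defined post-test and the four-point ANOVA risks comparing completers only

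*Protocol article*

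**What the plan says.** Study flow sets the visits: "At mid-treatment (that is, after 15 sessions), post-treatment (after 30 sessions), and 6-month follow-up, the neuropsychological assessments are repeated". The only statement of pace in the SCP section is "Participants are trained one to three times per week (maximum of five times per week) for a total of 30 sessions"; the NIRS section likewise gives one to three sessions per week and 30 in total. Neither sets a calendar date for the post-test. The Control group section follows the same logic for the healthy controls: "The time between the first and the second measurement is dependent on the amount of time it takes the matched patient to complete treatment".

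Ethics and written consent tells participants that "they have the right to discontinue their participation at any time without giving a specific reason and without penalty". It does not say whether stopping the training also ends the assessments.

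The Statistical analysis section states: "All dependent variables will be tested for effects within and between groups by an analysis of variance (ANOVA) (three groups x four assessment points". Randomization and blinding adds that "neither blinding of participants nor blinding of assessors was possible". The primary scales are the ADHS-SB, the FEA-AFB and the WRI. In Table 1 the first two are scheduled at screening, mid, post and follow-up. The WRI is scheduled at screening, post and follow-up only.

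**The concern.** A visit that falls due after 30 sessions has no due date for someone who stops at session 20. The ANOVA then has no place for that person's incomplete record if it is run in the usual way. Taken together, the visit rule and the model leave a comparison among those who persisted with training, no longer among those randomised.

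This trial is exposed to the problem. Participants know which signal they are training, the load is 30 sessions, and the primary scales are self-report, third-party rating and interview by unblinded assessors. It is plausible that stopping depends on arm and on perceived benefit. If it does so differently between arms, the contrast with EMG is shifted even when training has no specific effect. A later analysis plan can change the model, but it cannot recover ratings that were never collected.

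**Working it through.** **Inputs from the article.** Effect size 0.81, one-sided alpha 0.05, power at least 80%, n = 20 per arm (Sample-size calculation); 30 sessions at one to three per week, maximum five (SCP section). **Assumed, because the article gives no figure:** the share that stops, and how strongly stopping relates to change.

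**1. The plan's own figure.** For a one-sided two-sample t-test with n per arm, the noncentrality is 0.81 × √(n/2) on 2n − 2 degrees of freedom. At n = 20 this is 0.81 × √10 = 2.561 with 38 df and critical value 1.686, giving power 0.808. The stated 20 per arm reproduces, with almost no slack: at n = 19 power is 0.789.

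**2. Calendar time of the post-test.** 30/3 = 10 weeks, 30/1 = 30 weeks, and 30/5 = 6 weeks at the maximum pace. The session count therefore implies no usable date.

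**3. Loss of numbers.** If 20% stop in each arm and are not post-tested, 20 × 0.80 = 16 per arm remain, or 48 of 60. The noncentrality is 0.81 × √8 = 2.291 with 30 df and critical value 1.697, giving power 0.724. This treats the comparison as two arms at one time point, as the sample-size section does.

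**4. Shift of the contrast when there is no true effect.** Suppose an arm loses the 20% with the lowest stop score, and that score correlates ρ with change. In a large sample the mean change of those who remain rises by ρ × φ(z)/0.80, where z is the 20th percentile of the standard normal and φ(z)/0.80 = 0.35. For ρ = 0.3, 0.5 and 0.8 this is 0.105, 0.175 and 0.28 SD. Simulation with 20 per arm (40,000 runs) gives slightly less.

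| Whose poor responders leave (20% lost in each arm) | Shift in SD, active minus EMG, at ρ = 0.3 / 0.5 / 0.8 | One-sided 5% error becomes |
|---|---|---|
| Active arm; EMG loses at random | +0.10 / +0.17 / +0.27 | about 9% / 13% / 21% |
| EMG; active arm loses at random | −0.10 / −0.17 / −0.27 | about 3% / 2% / 1% |
| Both arms, same rule | about 0 | about 5% / 5% / 7% |

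At 10% loss per arm, the first row's error rates are about 7%, 9% and 12%.

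**The case against.** The strongest reply is that Study flow only describes the nominal path of a participant who follows the schedule. On this view, follow-up of stoppers, analysis sets and missing data belong in a full protocol or analysis plan that is not shown. Much of this stands. Their absence from a journal article is not a finding, and the consent wording sets no assessment policy either way. What remains is stated text: a visit rule expressed only in sessions, and a named model that does not suit incomplete records.

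A reader might go further and infer that stoppers never reach the endpoint visit, or that the analysis is a completers' analysis. The documents do not say so. Nothing forbids assessing stoppers, and no complete-case rule is written; dropping incomplete records is the classical default of the named model. A reader might also infer that the 6-month follow-up is counted from session 30, and so is lost as well. Its starting point is not stated.

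Two points on size also stand. Nothing in the article indicates which arm's poor responders would leave, so quoting only the inflated error rate would be selective. And multiplying independent loss rates over three visits would not describe this problem, where stopping removes the later session-timed visits together.

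Finally, timing assessments by training dose is defensible in a proof-of-principle study that asks whether adults learn self-regulation. That supports keeping session-based visits for those who train, but it does not supply a visit for those who stop.

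**Conclusion.** The point holds as a risk created by two stated choices. Followed as written, early stoppers have no defined post-test, and the classical form of the planned ANOVA would leave them out of the randomised comparison. With 20% stopping, power falls from 0.808 to 0.724. The possible shift runs from about zero to 0.27 SD in either direction, depending on whether stopping works differently between arms. All of this rests on assumed stopping rates and correlations. The change should be made while the trial is ongoing. Confidence is medium, because the full protocol may already provide for stoppers.

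**What to change.** **Statistical analysis.** Replace the ANOVA with a repeated-measures mixed model that analyses all randomised participants in their assigned group and uses incomplete records. Use the time points that each scale actually has; the WRI has no mid assessment. Report completers as a secondary analysis. The model alone is not enough: it relies on the missing values being predictable from what was observed, and someone who stops before session 15 would have only baseline values.

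**Study flow.** State that stopping training does not end assessment. Collect at least the ADHS-SB and FEA-AFB from stoppers, by mail if needed as is already done at screening, and the WRI where possible. Do this when their post-test and follow-up would have fallen due on the planned training schedule. Because pace varies, the expected dates need to be recorded at the start for each participant.

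Testing at the moment of stopping is simpler but worse. Someone who leaves after session 3 would be post-tested within weeks, against 10 to 30 weeks for completers at one to three sessions per week, so timing would be mixed up with stopping.

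**Cost.** A sentence or two on visits, a change of model, a few extra questionnaires or interviews, and an estimate that may be smaller than among completers. If all stoppers are assessed, the analysed number stays at 20 per arm and power at 0.808, provided the effect among all randomised is still 0.81.
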